## Abstract

**Background::**

Ozanimod, a sphingosine 1-phosphate receptor 1 and 5 modulator, was approved as a disease-modifying therapy for active relapsing-remitting multiple sclerosis (RRMS) in 2020 and for active ulcerative colitis in 2021. Long-term, real-world studies in a nonselective population are needed. OzEAN is an ongoing study to assess the real-world persistent use, effectiveness, and safety of ozanimod and its impact on quality of life (QoL) in patients with RRMS over a 5-year period.

**Methods:**

This prospective, noninterventional, postmarketing authorization study will enroll ~1,300 patients (≥18 years of age) with active RRMS. The decision to initiate ozanimod must have been made before and independent from study participation. Enrollment began in March 2021. Recruitment is ongoing and will last for 36 months across 140 sites in Germany. Treatment-naive patients or those having prior experience with a disease-modifying therapy receive oral ozanimod 0.92 mg/day after an initial dose escalation, per the summary of product characteristics recommendations, for up to 60 months. Persistence with ozanimod treatment (primary endpoint) is assessed at month 60. Secondary endpoints include additional physician-reported outcomes [persistence at earlier time points, annualized relapse rate, Expanded Disability Status Scale score, cognition (Symbol Digit Modalities Test), and incidence of adverse events], and patient-reported outcomes assessing patient satisfaction, adherence, and treatment modalities (Treatment Satisfaction Questionnaire for Medication, v1.4), disability (United Kingdom Neurological Disability Rating Scale), QoL (MSQOL-54 questionnaire), fatigue (Fatigue Scale for Motor and Cognitive Functions), and health economics [Work Productivity and Activity Impairment Questionnaire for Multiple Sclerosis (German v2.1); Multiple Sclerosis Health Resource Survey, v3.0]. A Multiple Sclerosis Documentation System with an internet-based e-health portal allows patients to view files and complete questionnaires. A safety follow-up will occur 3–8 months after the last ozanimod dose for patients who discontinue treatment early. Long-term results are anticipated after study completion in 2029. Yearly interim analyses are planned after enrollment has reached 25%.

**Conclusion:**

This is the first long-term, real-world study of ozanimod in patients with RRMS and, to our knowledge, the first noninterventional study utilizing a patient portal. These data will add to the safety/efficacy profile of ozanimod demonstrated in phase 3 trials.

**Clinical Trial Registration:**

Clinicaltrials.gov, identifier: NCT05335031.

## Introduction

Ozanimod is a sphingosine 1-phosphate receptor 1 and 5 modulator that blocks lymphocyte egress from lymphoid tissue, reducing the number of circulating lymphocytes in peripheral blood (1). Ozanimod was first approved in the United States in 2020 for the treatment of adults with relapsing forms of multiple sclerosis (RMS) and subsequently approved in multiple countries for adults with active relapsing-remitting multiple sclerosis (RRMS) defined by clinical or imaging results; in 2021, it was approved for the treatment of moderately to severely active ulcerative colitis in the United States and European Union (2, 3).

The ozanimod clinical development program in RMS (Figure 1) included a phase 1 pharmacokinetic/ pharmacodynamic trial (12 weeks), a phase 2 placebo-controlled trial (24 weeks) with a dose-blinded extension (24 months) (4, 5), and two phase 3 active-controlled trials, RADIANCE (24 months) (6) and SUNBEAM (minimum 12 months) (7). In both phase 3 trials, ozanimod 0.92 mg/day was associated with lower adjusted annualized relapse rate (ARR), fewer gadolinium-enhancing lesions and new or enlarging T2 lesions on brain magnetic resonance imaging (MRI), and reduced brain volume loss compared with intramuscular interferon β-1a 30 μg weekly (6, 7). The most frequent adverse events (AEs) associated with ozanimod treatment were upper respiratory infection, hepatic transaminase elevation, orthostatic hypotension, urinary tract infection, back pain, and hypertension. A pooled analysis of safety results from all trials, including an ongoing open-label extension study (DAYBREAK), were consistent with those of the phase 3 trials and demonstrated no new safety concerns (8). Patients in the parent trials were adults (18–55 years of age) with multiple sclerosis (MS) [diagnosed per 2010 McDonald criteria (9)] with a relapsing clinical course, brain MRI lesions consistent with MS, an Expanded Disability Status Scale (EDSS) (10) score of 0–6.0 (phase 1) or 0–5.0 (phase 2 and 3), and a history of relapses within the past 1–2 years (phase 2 and 3) (4, 6, 7).

**Figure 1 F1:**
[figure not shown]
Ozanimod clinical development in RMS program. ^a^In all trials, upon initiation of ozanimod, patients received 0.23 mg on days 1–4, 0.46 mg on days 5–7, and then their assigned dose of 0.46 or 0.92 mg on day 8 and thereafter. All patients entering the phase 2 dose-blinded extension period underwent dose escalation, even if treated with ozanimod in the parent trial, to maintain the blind. ^b^In DAYBREAK, dose escalation was performed for all patients entering from one of the active-controlled phase 3 trials, irrespective of prior treatment assignment (to maintain the blinding in the parent trials); dose escalation was not performed for those entering from the phase 1 or 2 trials, unless the last dose of ozanimod was >14 days before entering DAYBREAK.

Given the recent approvals of ozanimod, long-term studies in a non-selective, real-world population are not yet available, but are needed to evaluate ozanimod in a broader population of patients. Such studies could also provide information on persistence and adherence with ozanimod treatment, disease characteristics and treatment history of patients who are prescribed ozanimod, and patient-reported outcomes and pharmacoeconomic data, outcomes that were not evaluated in the clinical development program.

OzEAN is an ongoing prospective, non-interventional, postmarketing authorization observational cohort study to assess real-world persistent use, effectiveness, and safety of ozanimod, and the impact of treatment on quality of life (QoL), in patients with RRMS in Germany over a 5-year period. These real-world data, including patient-reported QoL outcomes, are of interest to German authorities and support their Health Technology Assessment (11).

## Methods and Analysis

### Study Setting and Treatment

Eligible patients will be enrolled in study sites across Germany. The decision to initiate ozanimod treatment must have been made by the physician before and independent from enrollment into the study. Patients receive oral ozanimod 0.92 mg/day for up to 60 months following a 7-day dose escalation regimen according to the summary of product characteristics (SmPC) (3). During this observation period, patients are evaluated at 16 data collection visits: baseline (visit 1), month 1 (visit 2), quarterly from month 3 to month 24 (visits 3–10), and at 6-month intervals from month 24 to month 60 (visits 11–16; Figure 2). Patients who permanently discontinue ozanimod treatment before month 60 are withdrawn from the observational study. A safety follow-up is performed when a new MS therapy is initiated (3–8 months after receiving the final dose of ozanimod) or 8 months (at the latest) after receiving the final dose of ozanimod if no new MS therapy is initiated.

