**Figure 2 F2:**
[figure not shown]
OzEAN study design. MS, multiple sclerosis; RRMS, relapsing-remitting multiple sclerosis. ^a^Days 1–4: ozanimod 0.23 mg; days 5–7: ozanimod 0.46 mg; days 8 and thereafter: ozanimod 0.92 mg. ^b^Patients who discontinue ozanimod prior to end of study (month 60) will be withdrawn from the OzEAN study and a safety follow-up will be performed 3–8 months after the last dose of ozanimod when a new therapy for MS is started or after 8 months (at the latest) if no subsequent MS therapy is initiated.

The individual study duration (observation period) per patient includes up to 60 months for the noninterventional treatment documentation period, and approximately 3–8 months for the safety follow-up period in case of premature discontinuation of ozanimod. The overall study duration is 104 months, including a 36-month recruitment period, 60-month observational period, and up to 8-month safety follow-up period. The entire study period is planned to last from the enrollment of the first patient (March 2021) until March 2029.

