**Safety assessment**						
AEs/SAEs	Assessed continuously throughout study					
Laboratory panel^h^	X^h^	X^h^	X^h^	X^h^		X^h^

*AE, adverse event; ARR, annualized relapse rate; EDSS, Expanded Disability Status Scale; FSMC, Fatigue Scale for Motor and Cognitive Functions; MRI, magnetic resonance imaging; MS, multiple sclerosis; MSFC, Multiple Sclerosis Functional Composite; MS-HRS v3.0, Multiple Sclerosis Health Resource Survey, version 3.0; MSQOL-54, Multiple Sclerosis Quality of Life-54; SAE, serious adverse event; SDMT, Symbol Digit Modalities Test; TSQM v1.4, Treatment Satisfaction Questionnaire for Medication, version 1.4; UKNDS, United Kingdom Neurological Disability Rating Scale; WPAI-MS v2.1, Work Productivity and Activity Impairment Questionnaire for Multiple Sclerosis, version 2.1*.

a *Documentation performed directly after a patient reached the regular end of study (at month 60) or permanently discontinued ozanimod treatment before month 60; if routine data were collected that do not meet any of the documentation time points offered, these data may be entered with the month 60 documentation*.

b *Follow-up documentation of potential AEs and subsequent therapy, performed approximately 3–8 months after stopping treatment with ozanimod and when a new MS therapy is initiated, or after 8 months (at the latest) if there is no subsequent MS therapy initiated*.

c *Includes MS diagnosis according to International Classification of Diseases, Tenth Revision; first manifestation of MS; course of MS disease and number of relapses within the year before enrollment; and type and duration of prior disease-modifying therapies for MS*.

d *Includes vital parameters, physical status*.

e *Treatment modalities referring to ozanimod, including (planned) date of first administration of ozanimod, reason for switch to ozanimod, interruptions, re-initiation of therapy following treatment interruption, and reason for discontinuation in case of switch to another MS treatment*.

f *At yearly intervals (months 12, 24, 36, 48, and 60) only*.

g *At 6-month intervals (months 6, 12, 18, and 24) only*.

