Medication adherence (secondary endpoint) will be evaluated categorically in terms of the percentage of doses taken as prescribed.

Secondary endpoints of clinical effectiveness (ARR, EDSS, and SDMT) and all PRO measures (changes from baseline, including proportion of patients who achieved a clinically meaningful change from baseline) will be analyzed descriptively. For TSQM v1.4, it is assumed that a clinically meaningful relationship between TSQM v1.4 domains and clinical outcomes is given if the effect size (Cohen's d) is > 0.3 (15).

All AE data will be listed and summarized. AEs will be classified using the Medical Dictionary for Regulatory Activities (MedDRA) classification system. The incidences based on the patient population enrolled as well as incidence density rates (number of events/sum of person-time in years) of all AEs, serious AEs (SAEs), adverse drug reactions (ADRs), and serious ADRs will be summarized by system organ class, preferred term, and relationship to study treatment. AEs leading to discontinuation from treatment will also be summarized and listed separately.

SAS software version 9.2 or higher will be used for analyses.

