### Monitoring

An external steering committee is planned for data review, data evaluation, and publication in agreement with the leading principal investigator.

An interim analysis will be conducted after enrollment of 25% of the planned number of patients and will describe the baseline data. Thereafter, yearly interim analyses are planned.

AEs are collected during study site visits and via the patient portal, as described previously. All AEs occurring after the first dose of ozanimod until the end of the study (including the safety follow-up), whether related or not to ozanimod treatment, will be recorded and reported to the sponsor or its designee. AEs and SAEs are reported within 24 h. If it is discovered that a patient or female partner of a male patient is pregnant, this is reported to the sponsor within 24 h. SAEs associated with the pregnancy are reported within 24 h. Follow-up information on pregnancy outcomes is forwarded to the sponsor, even if the outcome becomes known after the end of the study.

Representatives of the sponsor and/or its delegates are permitted to visit all study site locations to assess the data quality and study integrity. On site, they review study files and, if allowed by local laws and regulations, patient medical charts to compare them with source documents, discuss the conduct of the study with the investigator, and verify that the facilities remain acceptable. In addition, the study may be evaluated by the sponsor's internal auditors and government inspectors, who are permitted access to CRFs, source documents, other study files, and study facilities.

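### The safety follow-up rule cannot be met by patients who start a new therapy within 3 months of the last dose, and results up to that visit are not separated by treatment period

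*Protocol article*

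**What the plan says.** The timing of the safety follow-up is stated in four places in the protocol article:

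- Study Setting and Treatment: "A safety follow-up is performed when a new MS therapy is initiated (3–8 months after receiving the final dose of ozanimod"). For patients who start nothing else, the same section sets only an outer limit, 8 months from the last dose.
- Figure 2 legend: "a safety follow-up will be performed 3–8 months after the last dose of ozanimod when a new therapy for MS is started", again with 8 months as the limit if no therapy follows.
- Table 2, footnote b: "performed approximately 3–8 months after stopping treatment with ozanimod and when a new MS therapy is initiated", with the same 8-month limit.
- Abstract, Methods: "A safety follow-up will occur 3–8 months after the last ozanimod dose for patients who discontinue treatment early". No therapy trigger is mentioned.

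Switching is foreseen. Table 2 records subsequent MS treatment at the end of observation as well as at the safety follow-up, and footnote e includes the "reason for discontinuation in case of switch to another MS treatment".

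On adverse events, Monitoring covers "All AEs occurring after the first dose of ozanimod until the end of the study (including the safety follow-up"). Statistical Methods reports "incidence density rates (number of events/sum of person-time in years") for all AEs. Table 3 expresses AE incidence per person-time over a follow-up period whose limits it does not state.

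On effectiveness, Table 3 and Endpoints and Assessments list the safety follow-up as a time point for ARR, EDSS, SDMT and the patient-reported outcomes. ARR is relapses in all patients divided by their days in the study, times 365.

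**The concern.** Two things follow from the text.

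First, the start of a new therapy and the 3-to-8-month window agree only if the new therapy starts inside the window. If it starts earlier, a site must choose between them. Because AE recording runs to this visit, the choice also fixes how long that patient's events are collected and how much of the collection falls on the next drug.

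Second, the visit exists only for patients who stopped ozanimod. Its EDSS, SDMT and patient-reported values come from a selected group at varying times since the last dose, some already on a successor therapy. AEs and relapses from the same interval could be summed with on-treatment events. Safety and effectiveness of ozanimod are stated aims, so a reader needs to know which results were obtained on the drug.

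**Working it through.** **Timing, passages side by side.** Take a patient who stops ozanimod and starts another MS therapy 1 month later (an illustration).

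- Under the therapy trigger, the visit falls at month 1. That is outside the 3-to-8-month window in every statement of the rule.
- Under the window, the visit falls between month 3 and month 8, so 2 to 7 months after the new therapy began (3 − 1 and 8 − 1). It is then not held when that therapy is started.
- Footnote b joins the two conditions with a conjunction, and for this patient they cannot both be true. Its qualifier that the window is approximate softens the conflict without settling it.
- The 8-month limit applies only where no new therapy is started, so it does not help.

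**AE and relapse denominators.** Monitoring fixes when AEs are recorded. Statistical Methods and Table 3 give the form of the rate but not its risk window. Days in the study are also open to two readings. The text after the Figure 2 legend counts the safety follow-up within individual study duration, while Study Setting and Treatment says patients who stop are withdrawn from the observational study.

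**Effectiveness at the follow-up.** Tables 2 and 3 schedule relapse, EDSS and SDMT at this visit. The description of the visit in Data Collection Methods names AEs, subsequent treatment, concomitant medication and patient-reported outcomes, but not these three.

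**Size.** The plan gives no figure of its own to reproduce, so this is an illustration.

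Inputs from Sample Size and Recruitment: about 1,300 patients and 5-year persistence S = 0.55. Assumptions: non-persistence means permanent discontinuation, the discontinuation hazard is constant, no patient is lost, and each follow-up lasts 3 or 8 months.

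- Patients stopping: 1,300 × (1 − 0.55) = 585.
- Off-drug time: 585 × 3/12 = 146 person-years; 585 × 8/12 = 390 person-years.
- Hazard: −ln(0.55)/60 = 0.00996 per month.
- Mean time on drug: (1 − 0.55)/0.00996 = about 45.2 months.
- On-drug total: about 4,893 person-years (mean time × 1,300/12, unrounded mean).
- Off-drug share: 146/(4,893 + 146) = 2.9%; 390/(4,893 + 390) = 7.4%.

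The article expects persistence of 50% in switchers and 55% to 60% in treatment-naive patients. With S from 0.50 to 0.60 the share runs from 2.5% (S = 0.60, 3 months: 130 off, 5,090 on) to 8.5% (S = 0.50, 8 months: 433 off, 4,689 on).

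**Effect on a pooled AE rate at S = 0.55.** Suppose the off-drug rate is r times the on-drug rate and both events and time are pooled. The pooled rate relative to the on-drug rate is (on + r × off)/(on + off). For an 8-month follow-up:

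- r = 0.5: (4,893 + 195)/5,283 = 0.96.
- r = 2: (4,893 + 780)/5,283 = 1.07.

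For a 3-month follow-up the corresponding values are 0.985 and 1.029.

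**The case against.** The 3-to-8-month interval appears in all four statements, so a coherent reading exists: the visit always lies in that interval, is prompted by a new therapy, and takes place by month 8 if there is none. That is fair, and it means the gap is confined to patients who switch before month 3. No sentence says that the window overrides the trigger, however, so the gap is real for them. Divergence between sites is a reasonable expectation, not something the document shows.

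A reader might infer that off-drug and next-drug events certainly enter the ozanimod AE rates. The document does not support that. It fixes the recording window and leaves the risk window of the rate open. An on-treatment definition may stand in the full protocol or analysis plan, which are not shown. Collecting AEs after the last dose is the purpose of a safety follow-up and is no error. Summaries by relationship to treatment, and the separate reporting of adverse drug reactions, partly protect the reader, though the all-AE figures would not be protected.

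A reader might also take the 3% to 7% as the size of the timing conflict. It is not: it covers all follow-up time in all patients who stop.

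Finally, the safety follow-up is listed as its own time point, so its EDSS, SDMT and patient-reported values do not alter the scheduled month 6 to month 60 results, and the analyses are descriptive. That stands. The remaining risk is one of interpretation: those values could be read as ozanimod outcomes.

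**Conclusion.** The concern holds in a limited form. The timing statements conflict for patients who start a new MS therapy before month 3, and the document does not say which condition governs. As written, AEs through the safety follow-up are not separated from on-ozanimod events, the person-time is undefined, and effectiveness and patient-reported results are listed at a visit that only patients who stopped attend.

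Under the stated assumptions, off-drug follow-up is about 3% to 7% of total person-time, and the effect on overall AE rates is probably modest: 0.96 to 1.07 times the on-drug rate even if the off-drug rate is half or double. Loss to follow-up would lower the off-drug time. Single event types that cluster after stopping or under the next therapy could be affected more. The share of patients who switch before month 3 is not given, so the timing conflict itself cannot be sized.

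**What to change.** 1. Reconcile the Abstract, Study Setting and Treatment, the Figure 2 legend and Table 2 footnote b so that one rule states when the safety follow-up takes place for a patient who starts a new MS therapy before month 3. Which timing is right is for the sponsor to decide.
2. Report AE counts with person-time, and relapses with days for ARR, in three periods: on ozanimod, off ozanimod before any new MS therapy, and after a new MS therapy has started.
3. Show safety follow-up EDSS, SDMT and patient-reported values by whether a new therapy had started, labelled as post-discontinuation results.

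The split should need no new assessments, because ozanimod treatment and subsequent MS treatment are already documented. The cost is one clarified rule, period flags in the analysis data and a few more tables, some with small cells.

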**Figure 2 F2:**
[figure not shown]
OzEAN study design. MS, multiple sclerosis; RRMS, relapsing-remitting multiple sclerosis. ^a^Days 1–4: ozanimod 0.23 mg; days 5–7: ozanimod 0.46 mg; days 8 and thereafter: ozanimod 0.92 mg. ^b^Patients who discontinue ozanimod prior to end of study (month 60) will be withdrawn from the OzEAN study and a safety follow-up will be performed 3–8 months after the last dose of ozanimod when a new therapy for MS is started or after 8 months (at the latest) if no subsequent MS therapy is initiated.

The individual study duration (observation period) per patient includes up to 60 months for the noninterventional treatment documentation period, and approximately 3–8 months for the safety follow-up period in case of premature discontinuation of ozanimod. The overall study duration is 104 months, including a 36-month recruitment period, 60-month observational period, and up to 8-month safety follow-up period. The entire study period is planned to last from the enrollment of the first patient (March 2021) until March 2029.

### Eligibility Criteria

Eligible patients are adults (≥18 years of age) diagnosed with RRMS who are either treatment-naive or have prior experience with a disease-modifying therapy and elected to switch to ozanimod. Patients with contraindications specified in the current version of the SmPC (3), or with known hypersensitivity to ozanimod or any of its excipients, are excluded. Patients may not be participating in any other clinical studies.

Inclusion and exclusion criteria are shown in Table 1.

**Table 1 T1:** Eligibility criteria.

**Inclusion Criteria**	**Exclusion Criteria**
Males or females aged ≥ 18 years who provided written informed consent	Contraindications specified in the current version of the SmPC
Confirmed diagnosis of RRMS according to ICD-10 and eligible for treatment with ozanimod according to physician's judgement and based on the recommendation of the current SmPC	Known hypersensitivity to the active substance(s) or to any of the excipients of ozanimod as specified in the SmPC
The decision to initiate treatment with ozanimod must have been made by the treating physician before enrollment and independently of this study; retrospective documentation of ozanimod therapy and enrollment of patients that are already on ozanimod therapy is not allowed	Participation in any other clinical studies

*ICD-10, International Statistical Classification of Diseases and Related Health Problems, 10^th^ version; RRMS, relapsing-remitting multiple sclerosis; SmPC, Summary of Product Characteristics*.

